## Abstract

**Background:**

The ‘common variant, common disease’ model predicts that a significant component of hereditary breast cancer unexplained by pathogenic variants in moderate or high-penetrance genes is due to the cumulative effect of common risk variants in DNA (polygenic risk). Assessing a woman’s breast cancer risk by testing for common risk variants can provide useful information for women who would otherwise receive uninformative results by traditional monogenic testing. Despite increasing support for the utility of common risk variants in hereditary breast cancer, research findings have not yet been integrated into clinical practice. Translational research is therefore critical to ensure results are effectively communicated, and that women do not experience undue adverse psychological outcomes.

**Methods:**

In this prospective study, 400 women with a personal and/or high risk family history of breast cancer will be recruited from six familial cancer centers (FCCs) in Australia. Eligible women will be invited to attend a FCC and receive their personal polygenic risk result for breast cancer. Genetic health professionals participating in the study will receive training on the return of polygenic risk information and a training manual and visual aids will be developed to facilitate patient communication. Participants will complete up to three self-administered questionnaires over a 12-months period to assess the short-and long-term psychological and behavioral outcomes of receiving or not receiving their personal polygenic risk result.

**Discussion:**

This is the world’s first study to assess the psychological and behavioral impact of offering polygenic risk information to women from families at high risk of breast cancer. Findings from this research will provide the basis for the development of a new service model to provide polygenic risk information in familial cancer clinics.

**Trial registration:**

The study was retrospectively registered on 27th April 2017 with the Australian and New Zealand Clinical Trials Group (Registration no: ACTRN12617000594325; clinical trial URL: https://www.anzctr.org.au/Trial/Registration/TrialReview.aspx?id=372743).

**Electronic supplementary material:**

The online version of this article (doi:10.1186/s12885-017-3485-0) contains supplementary material, which is available to authorized users.

## Background

Breast cancer is the greatest cause of premature death in Australian women, accounting for approximately 12% of all premature deaths [1]. Between 10% and 20% of breast cancer is associated with a family history of breast and/or related cancers (termed hereditary breast cancer) [2]. Hereditary breast cancer is clinically important due to the availability of effective risk management strategies that can be targeted to certain subgroups of high-risk women (e.g. breast magnetic resonance imaging and risk-reducing surgery) [3–5].

Since familial cancer clinics (FCCs) were first established in Australia in the early 1990’s, clinical practice has focused on the molecular diagnosis of high-penetrance (*BRCA1/2, TP53, PTEN*) and moderate-penetrance (*PALB2, RAD51C, BRIP1*) pathogenic gene variants, which were discovered through family linkage or candidate gene approaches. However, current testing only identifies a pathogenic gene variant in fewer than 25% of families tested [6], meaning that the majority of families where the risk of hereditary breast cancer is assessed as potentially high receive ‘uninformative’ genetic test results. In these cases the final risk assessment and screening advice is not personalized, but rather based on empiric family history data and extrapolated from population epidemiological studies [7].

The ‘common variant, common disease’ model predicts that a significant component of hereditary breast cancer that cannot be explained by moderate or high-penetrance pathogenic gene variants is due to the cumulative effect of multiple common risk variants in DNA (single nucleotide polymorphisms, SNPs) [8–12]. Individually, each of these common risk variants has only a minimal effect on breast cancer risk, however, when considered altogether, the combined effect is responsible for large differences in risk for different individuals in the population that includes a significantly increased risk for some women. To date more than 96 risk-associated SNPs have been found in large high-quality breast cancer genome-wide association studies [13–16].

The combined effect of common variants is most commonly expressed as a Polygenic Risk Score (PRS). Typically this is calculated by multiplying the risk associated with each SNP that an individual carries, expressed as the per-allele odds ratio, or more commonly adding together the log-odds ratio. Sawyer et al. [9] examined the distribution of the PRS and its clinical implications in the familial breast cancer setting. For this study, breast cancer risk was modeled by genotyping of 22 breast cancer–associated common variants. The study considered a cohort of 954 women with a personal and family history of breast cancer in which a high-risk *BRCA1* or *BRCA2* pathogenic variant had been excluded, and divided them divided into high, intermediate and low polygenic risk groups based on the quartiles of the distribution of the PRS, where the second and third quartiles formed the intermediate risk group. When the features of the three groups were compared, significant differences were identified in the frequency of early-onset and second primary breast cancers. Based on a population lifetime risk of breast cancer of 1 in 11 (9%), the difference in relative risk between low PRS and high PRS was a greater than 4.5-fold, which is equivalent to an average absolute life time breast cancer risk of 6% in the low PRS group and 27% in the high PRS group. Additionally, compared to women with a low PRS, women in the high PRS group had an increased frequency of early onset breast cancers before age 35 years, an approximate two-fold increase in the rate of a contralateral breast cancer, less than half the risk of a *BRCA1/2* mutation, and no increased risk of ovarian cancer [9]. Similar findings have since been reported in additional studies that have incorporated a larger number of common risk variants and combination with risk prediction models [8, 10–12]. In all instances, PRS results have been found to provide a more accurate risk prediction of breast cancer risk than by family history alone.

Current Australian eviQ and UK NICE guidelines recommend enhanced surveillance and risk management strategies for women with a lifetime risk of developing breast cancer over 17% [17, 18]. Thus, women identified as having a high PRS would be eligible for additional risk management strategies, including regular breast screening from a younger age and risk-reducing medication. Additionally, women with a personal history of breast cancer and a high PRS should also be advised about increased risk for contralateral breast cancer and appropriate risk management strategies, including risk-reducing medication if not otherwise indicated by their primary breast cancer pathology, and mastectomy in place of breast conservation. Women who are assessed as intermediate risk by PRS can be advised that their result does not significantly alter their breast cancer risk status, and hence risk management advice is not altered. In contrast, unaffected women assessed as low risk by PRS, can be reassured that population screening levels are appropriate. Where a diagnosis of breast cancer does occur in this group, the lower risk of a second primary cancer may help some women to have confidence to opt for breast conservation. It is important to note however, that for women with a personal diagnosis of breast cancer, a low PRS result does not exclude the possibility of another genetic contribution to their personal history of cancer.

### Psychosocial and Behavioral Outcomes:

The majority of published studies assessing the psychosocial impact of genetic testing for cancer susceptibility have focused on families with a known pathogenic variant in the *BRCA1/2* genes. These studies reported that the uptake of *BRCA1/2* genetic testing is more consistently related to psychological factors (i.e. cancer anxiety and perceived risk) than to sociodemographic variables [19]. Studies on the psychological impact of *BRCA1/2* genetic testing among women demonstrate that non-carriers derive significant psychological benefits from genetic testing and experience few adverse psychological effects, while for carries, distress increases shortly after receiving results but returns to pre-testing levels over time [19–22]. However, one study reported strong declines in well-being in affected women after receipt of testing results [23], indicating that the impact of testing in people affected by cancer is amplified by their experience of cancer.

Regarding its impact on health behaviors, one review article concluded that genetic testing for breast cancer susceptibility is associated with increased adherence to recommended screening and uptake of risk-reducing surgery in affected carriers [24]. In contrast, for those where genetic testing leads to an uninformative test result, studies have reported low uptake of medical and surgical intervention [24]. Further studies in this population have identified that a minority of affected women misinterpret their negative result as meaning that the cancers in their family were definitely not caused by a gene mutation, and hence may feel falsely reassured by their results as ‘No news is good news’ [25]. Thus, testing for common risk variants has the potential to provide personalized risk management recommendations for a significant proportion of at-risk women who would otherwise receive an uninformative result.

To date there has been little research on the uptake and effective communication of this complex polygenic information in the hereditary cancer setting. Early research has been primarily based on hypothetical scenarios assessing interest and attitudes towards testing for common risk variants. These studies have reported a strong interest in polygenic risk testing with interest ranging from 74% to 78% [26–30]. Similarly to uptake of *BRCA1*/2 testing, interest was more consistently related to psychological factors (i.e. perceived risk and greater cancer worry), rather than sociodemographic variables [26–30]. Only two studies have assessed actual uptake of testing and associated outcomes [31, 32]. These studies offered testing for common risk variants associated with colorectal cancer risk; however, they were limited by the small number of variants tested and hence the associated cancer risk was uncertain. The authors concluded that the behavioral changes observed (improvement in diet and exercise) were a result of the genetic counselling, which emphasized lifestyle factors associated with colorectal cancer risk, rather than a result of the polygenic risk information.

Despite increasing support for the utility of common risk variants in hereditary breast cancer [8–12], research has not yet been integrated into clinical practice. Testing for polygenic risk in breast cancer is not currently available in any clinical setting, or currently considered for return to patients outside of a research setting by any FCCs in Australia or internationally. This reflects the status of polygenic risk as an emerging technology and the limited amount of information available on the outcomes of offering such testing. Translational research is needed to develop a model of genetic counselling for polygenic breast cancer risk, which addresses the psychosocial needs of patients and assists health professionals in communicating these complex results to patients.

### Common genomic variants and familial cancer cohort

The Common Genomic Variants and Familial Cancer Study (commonly known as: the Variants in Practice study, ViP) provides a unique cohort in which to systematically ascertain the important psychosocial and clinical implications of testing for polygenic risk and answer a large number of research questions at a small cost [9]. The cohort consists of over 4400 men and women from Victoria and Tasmania, Australia, who have a high-risk family history of breast cancer. Prior to enrolment in the study, all index cases will have attended a participating FCC and undergone clinical assessment, including molecular testing of *BRCA1/2* and other genes depending on their family history and phenotype. Unlike index cases, only a small proportion of family members have a personal history of cancer and most have not attended a FCC. To date 3700 of the total study cohort have had genomic testing for 96 SNPs already known to be associated with breast cancer risk.

### Clinical challenge

The information arising from polygenic risk factors is fundamentally different in nature to testing for monogenic high-penetrance genes, which has traditionally formed the basis of the information provided in FCCs. For example, the interpretation of polygenic risk requires greater consideration of the context, including the individual’s personal and family history, and whether testing for monogenic high-penetrance genes has occurred. In addition, the nature of polygenic inheritance means that breast cancer risk will be present for some women in the absence of a familial pattern. Translational research is critical to ensure that results are effectively communicated, in a way that allows improved risk management strategies to be implemented without undue adverse psychological outcomes. This translational study aims to develop a best-practice model of providing polygenic risk results in the hereditary breast cancer setting, to meet the likely future demand for, and prepare for widespread implementation of genomic testing in this setting.

## Methods/design

### Study objectives and hypotheses

The study will invite 400 female participants from the ViP study (including a mixture of index cases and family members) to receive their personal PRS results and will examine the following aims and hypotheses:

**Aim 1.** To determine the interest in polygenic risk assessment and investigate the determinants of accepting this invitation to receive results, i.e. uptake of this offer and factors associated with uptake.

Hypothesis 1a) Compared to women who decline their results (‘decliners’), women who receive their results (‘receivers’) will:i.have higher baseline breast cancer anxiety (primary outcome variable), a need to avoid uncertainty, and they will be more likely to have daughters;ii.be more likely to comply with breast cancer screening guidelines 12 months after receiving their results.

**Aim 2.** Assess the short-(2 weeks) and long-term (12 months) psychological and behavioral outcomes, including compliance with recommended screening and preventative strategies, of ‘receivers’ and ‘decliners’.

Hypothesis 2a) Receivers with a high PRS result will:i.have increased breast cancer anxiety compared to baseline in the short-term (2 weeks after receiving results), but breast cancer anxiety will return to baseline levels in the long-term (12 months after receiving results); and.ii.be more likely to report having implemented risk-reducing strategies 12 months after receiving their results when compared to receivers with a low PRS.

Hypothesis 2b) Unaffected women receiving a low PRS will have decreased breast cancer anxiety 2 weeks after receiving results, which will be sustained at 12 months, compared to affected women who receive a low PRS.

Hypothesis 2c) Affected women who receive a high PRS result will exhibit larger increases in breast cancer anxiety from baseline in the short-term (2 weeks after receiving results), compared to unaffected women who receive a high PRS.

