### Study design

Assessing a woman’s breast cancer risk by profiling common risk variants represents a novel approach in clinical genetics. The PRS results referred to in the protocol are research results obtained from the ViP study and will only be available to the 400 women invited to participate in this psychosocial study.

This is a prospective study which is being conducted across FCCs in two Australian states (Victoria and Tasmania). The study has been approved by the Peter MacCallum Cancer Centre Ethics Committee (HREC/16/PMCC/2) and the Tasmanian Health and Medical Human Research Ethics Committee (H0016395).

The primary psychological outcome measurement is breast cancer anxiety as assessed by the Impact Event Scale (IES). The secondary psychological and behavioral outcomes are: i) general anxiety and depression, ii) test-related distress, positive experiences and uncertainty, iii) concordance with screening guidelines, iv) uptake of preventative strategies, and v) level of decisional regret. The method of determining the PRS has been described elsewhere [9].

Data will be collected through self-reported questionnaires. Over the course of the study, participants will complete up to three questionnaires. Women who choose to receive their PRS result will complete three questionnaires: at baseline (prior to attending the FCC), two weeks after receiving their PRS result, and 12 months after receiving their result. Women who choose not to receive their result will complete two questionnaires: at baseline and 12 months after enrolment in the study (Fig. 2).

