#### Measures

Women will complete the three self-administered questionnaires over a 12-month period (see Additional file 1). A summary of the measures included at each time point is shown in Table 1.

**Table 1 Tab1:** Measures selected for study and corresponding questionnaires

Measure	Q1 Baseline	Q2 Receivers	Q3 Receivers	Q3 Decliners
Predictor Variables				
1. Demographic characteristics	√			
2. Protection motivation	√			
3. Perceived severity of breast cancer	√			
4. Response efficacy	√			
5. Response cost	√			
6. Self-efficacy	√			
7. Uncertainty avoidance	√			
Confounding Variable				
8. Stressful life events	√		√	√
Predictor and Outcome Variables				
9. Perceived breast cancer risk	√	√	√	
10. Knowledge of familial breast cancer and polygenic risk	√	√	√	
11. Breast cancer anxiety	√	√	√	√
Outcome Variables				
12. General anxiety and depression	√	√	√	√
13. Concordance with screening guidelines	√		√	√
14. Intention to take up and actual uptake of preventative strategies	√	√	√	√
15. Regret over testing decision		√	√	√
16. Recall and interpretation of results		√	√	
17. Test-related distress, positive experiences and uncertainty		√	√	
18. Reasons for declining results				√

Clinical data available through the ViP study includes: number of affected first- and second-degree relatives, including number deceased due to breast cancer, personal history of breast cancer, and for affected women, time since diagnosis.

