#### Statistical analyses

For each of the main outcome variables (e.g. breast cancer anxiety), linear or logistic regression will be used as appropriate. Further multivariable analyses will be used to adjust for potential confounding variables (e.g. age, parity, stressful life events). Appropriate regressions will be performed to investigate whether outcomes differ between receivers and decliners (hypothesis 1a) and between subgroups of affected and unaffected women (hypothesis 2c) and those receiving either a low or high PRS (hypothesis 2b and 2c). Repeated measurements will be analyzed using linear mixed models to assess how outcomes change over time among receivers (hypothesis 2ai and 2b). This approach adjusts for the repeated measures per person and also allows for missing values.

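### Hypothesis 1a(ii) compares screening compliance in self-selected groups at 12 months without stating that baseline compliance, collected in both groups, will be used, so a prior gap could be read as confirmation

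*Protocol article*

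**What the plan says.** Under Study objectives and hypotheses, 1a(ii) says that receivers, compared with decliners, will "be more likely to comply with breast cancer screening guidelines 12 months after receiving their results". It does not mention baseline. Other hypotheses in the same section do: 2a(i) says that high-score receivers will "have increased breast cancer anxiety compared to baseline in the short-term", and 2c speaks of "larger increases in breast cancer anxiety from baseline in the short-term".

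The Study design section makes clear that each woman decides whether to receive her result. On decliners it says: "Women who choose not to receive their result will complete two questionnaires: at baseline and 12 months after enrolment in the study". Receivers also complete a baseline questionnaire. In Table 1 (Measures), the row "13. Concordance with screening guidelines" is ticked for the baseline questionnaire and for the 12-month questionnaire of both receivers and decliners.

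For the analysis, the Statistical analyses section says: "Appropriate regressions will be performed to investigate whether outcomes differ between receivers and decliners (hypothesis 1a". Further multivariable models are to adjust for confounders, with age, parity and stressful life events given as examples. Linear mixed models are to be used "to assess how outcomes change over time among receivers (hypothesis 2ai and 2b".

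**The concern.** Receivers and decliners are not randomised. Hypothesis 1a(i) itself expects them to differ beforehand in breast cancer anxiety, attitude to uncertainty and having daughters. It is plausible that women who accept a risk result already attend screening more often. A comparison at 12 months alone then mixes two things: who chooses results, and what happens after results are given.

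Screening compliance is one of the study's main behavioural outcomes, and Aim 2 names it as an outcome for both groups. A significant 12-month difference is therefore likely to be read as a consequence of receiving results. The measurement that would help most to separate the two explanations is already collected in both groups, but the article does not say that it will be used for this comparison.

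**Working it through.** **What the text fixes.** The contrast in 1a(ii) is between groups at one time point. The method assigned to 1a is a regression of outcome on group. The only longitudinal model named is confined to receivers and to 2a(i) and 2b. Baseline concordance exists in both groups but is not named in the hypothesis, in the 1a analysis or among the example confounders.

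**Inputs from the article.** Sample size and power gives 215 receivers and 105 decliners completing (215 + 105 = 320 = 400 × 0.8) and a two-sided 5% level. It states no power or rate for 1a(ii), so there is no figure to reproduce.

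**Assumed inputs.** Compliance of 60% in decliners at baseline and 70%, 75% or 80% in receivers. Receiving results has no effect.

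**Step 1: the gap persists unchanged.** SE = √[p₁(1−p₁)/215 + p₀(1−p₀)/105], z = (p₁−p₀)/SE, and the chance of significance is Φ(z − 1.96).

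- 70% v 60%: SE = √(0.21/215 + 0.24/105) = 0.0571; z = 1.75; chance 42%.
- 75% v 60%: SE = √(0.1875/215 + 0.24/105) = 0.0562; z = 2.67; chance 76%.
- 80% v 60%: SE = √(0.16/215 + 0.24/105) = 0.0550; z = 3.63; chance 95%.

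A second power routine for two proportions gave 43% and 78% for the first two cases.

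**Step 2: some women change status.** Suppose that 12-month compliance depends only on baseline compliance, and that a proportion s of women keep their baseline status. The gap then shrinks by the factor 2s − 1. For 70% v 60% and s = 0.8, the 12-month rates are 0.7×0.8 + 0.3×0.2 = 62% and 0.6×0.8 + 0.4×0.2 = 56%, so 10 points become 6. With s = 0.9 they become 8. Each case was simulated 1,500 times and analysed by logistic regression, with and without the baseline value. A study counts as confirming 1a(ii) if the difference is significant and receivers are higher.

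| Baseline, receivers v decliners | Step 1: gap unchanged | 90% keep status, unadjusted | 80% keep status, unadjusted | Baseline in model (90% / 80%) |
|---|---|---|---|---|
| 70% v 60% | 42% | 29% | 16% | 2.3% / 2.7% |
| 75% v 60% | 76% | 54% | 35% | 2.9% / 3.1% |
| 80% v 60% | 95% | 82% | 56% | 2.3% / 2.1% |

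The nominal rate for a false finding in one direction is 2.5%. The adjusted results agree with it within simulation error. They are a best case by construction, because in the simulation the groups differ only through measured baseline compliance.

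**The case against.** The strongest objection is that silence is not a decision. The confounders are given as examples, so nothing excludes baseline concordance. The article condenses a fuller plan, and collecting the item at baseline in both groups is consistent with an intention to use it. This stands. A reader might infer that the study has decided not to use the baseline value, or that 1a(ii) is bound to confirm itself. The documents support neither. They show only that the use of baseline is not stated and that the hypothesis as worded does not require it.

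The restriction of the mixed models also proves little by itself. Those models are linear and concordance is categorical, so their scope does not settle which covariates enter a logistic model.

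1a(ii) also sits under Aim 1, on factors associated with uptake, and can be read as pure description. A persisting difference would then be a true answer. That reading is possible but strained: behaviour 12 months after a result cannot be a determinant of accepting it, and Aim 2 lists compliance among the outcomes. The ambiguity is itself a reason to state what the comparison is meant to show.

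Finally, the magnitude rests on assumed rates, all with receivers screening more beforehand. With no prior gap there would be no such inflation, and a reverse gap would hide a real difference. The unadjusted figures also take no account of the planned adjustment for other confounders. This stands too, so the percentages show what could happen, not what is expected.

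**Conclusion.** The point holds as a weakness in how 1a(ii) is specified, not as a demonstrated error in the analysis. The hypothesis fixes a 12-month comparison between self-selected groups without reference to baseline, while the article ties other hypotheses to baseline and collects the needed measurement in both groups. Followed as worded, the comparison cannot separate prior screening habit from later compliance.

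Under the assumed gaps of 10 to 20 points and no effect of receiving results, a prior difference alone gives a significant 12-month result in about 42–95% of studies if it persists fully, and in about 16–82% if 10–20% of women change status. Including baseline concordance brings false confirmation to about 2–3%, provided that no other difference between the groups drives compliance. The true compliance rates and the true prior gap are unknown. The primary outcome, breast cancer anxiety, is not affected by this point.

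**What to change.** Specify the test of 1a(ii) as a logistic regression of 12-month concordance on group (receiver or decliner), with baseline concordance as a covariate alongside the planned confounders. Show the cross-table of baseline by 12-month concordance separately for receivers and decliners.

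State that the unadjusted 12-month difference does not by itself show a consequence of receiving results, and that residual self-selection remains after adjustment. Choose the model in advance: a group-by-time analysis estimates a different quantity in groups that differ at baseline and is not an interchangeable alternative.

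In the same revision, align the time anchor. The hypothesis counts 12 months from receipt of results, whereas decliners are assessed 12 months after enrolment.

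The cost is a few sentences of analysis wording and one table. No new data and no change for participants are needed. If the analysis plan already contains this adjustment, a cross-reference is enough.

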### Participants

#### Inclusion criteria

Approximately 400 women will be recruited to this study from the existing ViP cohort. Only women aged 18 years will be recruited. Both index cases and their affected and unaffected family members will be invited to participate in this study. Women will be eligible if they have either a low (*N* = 200) or a high PRS (*N* = 200). Each group will be stratified by disease status, such that about 100 affected and 100 unaffected women are included in each study group (Fig. 3).

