#### Outcome variables

12.
*General anxiety and depression:* will be assessed using the Hospital Anxiety and Depression Scale (HADS). The 14-item HADS is a widely used measure of emotional disturbance and has two subscales measuring general anxiety and depression [40]. Each question has four possible responses, with responses scored on a scale from 0 to 3. A total scale score is obtained by summing each item (range 0 to 42) with a higher score indicating more general anxiety and depression.13.
*Concordance with screening guidelines* – six items have been developed in concordance with national guidelines for mammography and clinical breast examination [41] screening using the approach used in a previous study [42]. Participants will be categorized in terms of their concordance to the current screening guidelines.14.
*Intention to take up and actual uptake of preventative strategies –* 15 items have been developed to assess intention and uptake of preventative strategies, including risk-reducing surgery (bilateral mastectomy), medication (i.e. tamoxifen and raloxifen), and lifestyle factors (i.e. alcohol consumption, and exercise).15.
*Regret over testing decision* – will be assessed using the five-item Decision Regret Scale, which correlates with decisional conflict and quality of life [43].16.
*Recall and interpretation of testing results* – three items have been developed to assess recall and understanding of testing results.17.
*Test-related distress, positive experiences and uncertainty –* this measure includes 19 items from a validated questionnaire, the Multidimensional Impact of Risk Assessment Scale [44], assessing distress (six items), positive experiences (four items), and uncertainty (nine items) about genetic testing. Response options range from ‘never’ (0) to ‘often’ (5) with higher scores indicating higher psychological distress.18.
*Reasons for declining results* – will be assessed with 15 items used in a previous study [18]. Women will be asked to indicate the extent to which possible reasons for declining to receive results apply to them.

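### Hypothesis 2a(ii) is worded as strategies in place at 12 months, not uptake since disclosure, so earlier cancer treatment and existing habits can count as implemented

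*Protocol article*

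**What the plan says.** Under Study objectives and hypotheses, the population of 2a(ii) is given by "Receivers with a high PRS result will", with no restriction by disease status. The outcome is to be "more likely to report having implemented risk-reducing strategies 12 months after receiving their results", with low-PRS receivers as the comparison. The neighbouring anxiety hypotheses are written as change: 2a(i) and 2c refer to baseline, and 2b speaks of a decrease. Hypothesis 2a(ii) has no such reference.

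Inclusion criteria fixes the mix of women: "about 100 affected and 100 unaffected women are included in each study group".

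Outcome variables, item 14, describes 15 items on intention and uptake, "including risk-reducing surgery (bilateral mastectomy), medication (i.e. tamoxifen and raloxifen), and lifestyle factors". Table 1 lists item 14 at Q1, at Q2 and at both versions of Q3, so a baseline value exists.

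The main-text Background recognises that treatment and prevention overlap. For women with a personal history and a high PRS it mentions "risk-reducing medication if not otherwise indicated by their primary breast cancer pathology".

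Statistical analyses assigns the linear mixed model for change over time to 2a(i) and 2b. It ties the subgroup regressions to 2b and 2c, and gives age, parity and stressful life events as example confounders. It does not name 2a(ii), and links neither baseline uptake nor disease status to it.

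**The concern.** A woman treated for breast cancer before the study may already have had both breasts removed, or may already be taking tamoxifen. At 12 months she can truthfully report that strategy as implemented, although the PRS result changed nothing. For surgery she can no longer take it up at all. The same holds, for affected and unaffected women alike, for exercise or alcohol habits that predate Q1.

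A status comparison therefore mixes what was in place before disclosure with the response to disclosure. If the earlier part is equal in the two PRS groups, it adds events that carry no information and shrinks the contrast. If it is unequal, it shifts the contrast. 2a(ii) is the only hypothesis that compares uptake of risk-reducing strategies between PRS groups, so the study's reading of that behaviour rests on this definition.

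**Working it through.** **The plan's own figures.** The article states no uptake rate, effect size or power for 2a(ii), so there is no figure to reproduce for it. The completer count does reproduce: 400 × 0.80 = 320 = 215 receivers + 105 decliners.

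**Inputs from the article.** 215 receivers complete the study. About half of each PRS group is affected at invitation. Tests are two-sided at 5%.

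**Assumed inputs.** Receivers split evenly by PRS (215/2 = 107.5 per group) and by disease status (about 54 per cell). The rates of new uptake and prior treatment are also assumed. Prior use is placed in affected women only, so lifestyle habits already in place are left out.

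**Model.** Let *u* be the probability of new uptake among women who could still take the strategy up, and *q* the share of affected women who already had it. The share reporting it as implemented at 12 months is

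0.5 × [q + (1 − q) × u] + 0.5 × u = u + 0.5 × q × (1 − u).

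**(a) Equal prior use, true effect present.** The difference between PRS groups becomes (u_high − u_low) × (1 − 0.5q). Take u = 25% v 10%. Power is from a two-proportion z test with 107.5 per group.

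| q in both groups | High v low PRS, status | Difference | Power |
|---|---|---|---|
| 0% | 25.0% v 10.0% | 15.0 points | 83% |
| 20% | 32.5% v 19.0% | 13.5 points | 62% |
| 40% | 40.0% v 28.0% | 12.0 points | 46% |
| 60% | 47.5% v 37.0% | 10.5 points | 34% |

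**(b) Unequal prior use, no true effect.** With u = 10% in both groups, the difference is 0.5 × (1 − 0.10) × gap = 0.45 × gap. A 10-point gap in *q* gives 4.5 points and a 20-point gap gives 9.0 points.

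Example with 54 per cell and q = 35% v 25%:

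- High PRS: (54 × 0.35 + 54 × 0.65 × 0.10 + 54 × 0.10)/108 = 27.81/108 = 25.8%.
- Low PRS: (54 × 0.25 + 54 × 0.75 × 0.10 + 54 × 0.10)/108 = 22.95/108 = 21.3%.
- Odds ratio: (0.2575/0.7425)/(0.2125/0.7875) = 1.29.

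With *q* in the low-PRS group between 20% and 60%, the two-sided rejection rate is 10 to 13% for a 10-point gap and 27 to 34% for a 20-point gap. With no gap it is 5%.

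**(c) What restriction to new uptake gives back.** If women who already had the strategy are removed, 107.5 × (1 − 0.5q) remain per group: 96.75, 86 and 75.25 for q = 20, 40 and 60%. The same test of 25% v 10% then has power of 79, 74 and 68%. The 83% is therefore not fully recovered, but each value is well above its counterpart in (a).

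**The case against.** The strongest reply is that the article is a condensed account and fixes no scoring rule. The 15 items are in Additional file 1, which is not shown. They may ask about strategies started since the result, or separate treatment from prevention. Item 14 is asked at Q1, and the confounder list is open-ended. This stands in part: one cannot say that prior treatment *is* scored as a response, only that the wording allows it. It does not remove the point, because the hypothesis itself states the quantity to be compared, and it is status. Collecting item 14 at Q1 makes the remedy feasible; nothing in the article says it is used for 2a(ii).

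A reader might go further and infer that prior treatment is more common in the high-PRS group, so that the error favours the hypothesis. The Background does report "an approximate two-fold increase in the rate of a contralateral breast cancer" for high against low PRS, together with more early-onset disease. That makes more prior bilateral surgery plausible. But no section gives treatment rates by PRS, and nothing links PRS to endocrine medication. Stratified invitation balances affected status, though not necessarily among those who accept, nor treatment within the affected. The directional claim is therefore not supported.

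Three further limits stand. The surgery named is bilateral mastectomy, so unilateral treatment mastectomy is not at issue. Lifestyle items remain open to nearly all women and may supply much of any uptake, which the illustration omits. Preventive uptake is a secondary outcome; the primary psychological outcome is IES anxiety.

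**Conclusion.** The point holds as a defect in how the endpoint is worded. Read literally, 2a(ii) compares what women have in place at 12 months, in a sample about half of whom have had breast cancer, and does not isolate uptake after disclosure.

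Dilution needs no difference between PRS groups; it arises whenever some women already had a counted strategy. Bias does need a difference in prior use, which is possible but not shown. The magnitudes rest on assumed uptake and prior-treatment rates and an even split of receivers, so they show scale and are not estimates. The matter deserves correction because the remedy is cheap, but it concerns a secondary outcome and leaves the IES analyses untouched.

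**What to change.** Reword 2a(ii) so that the endpoint is uptake new between Q1 and Q3, and name the Q1 answers to item 14 as the reference.

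- **Surgery and medication:** analyse each strategy among women who had not already had it at Q1.
- **Lifestyle items:** use change from Q1, or adjust for the Q1 value.
- **Disease status:** adjust for it or report results by it. Unaffected women give the contrast least mixed with cancer treatment.
- **Check the instrument:** confirm that the Q1 items record strategies already in place, including those received as cancer treatment. The ViP data listed under Measures give personal history and time since diagnosis, but not treatment, so the Q1 answers must carry this.

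The change is to wording and analysis, with no new data collection if the Q1 items serve. The price is a smaller denominator for surgery and medication among affected women, and less precise subgroup estimates, with about 54 receivers per PRS-by-disease cell before any restriction.
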